### Statistical analysis

Covariate balance between matched exposed and unexposed participants will be examined. Unbalanced covariates will be included in the model as separate covariates. Other covariates that do not influence exposure but influence outcomes or reflect health-seeking behaviour alone may be included in the model after evaluating their balance between exposed and unexposed groups. These are the following:

Number of GP consultations in the 12-month period preceding cohort entry.Number of hospital outpatient referrals in the 12-month period preceding cohort entry.Number of hospital admissions in the 12-month period preceding cohort entry.Total number of GP consultations for knee or hip injury prior to cohort entry.Non-osteoporotic fractures, defined as fractures in any bone except the femur, distal radius and vertebrae, after the age of 18 years but before the age of 50 years in women and 60 years in men. This is a surrogate for physically active occupation or lifestyle that may associate with incident osteoarthritis.

Participants will enter the cohort on the index date, and data will be censored at the earliest of an event, study end date (31 December 2017), date of death, transfer out of CPRD for all outcomes, and additionally date of the last prescription of β-adrenoreceptor blocking drugs, plus 4 weeks (usual duration of GP prescription in the UK) for incident osteoarthritis, incident knee or hip pain, or new analgesic prescription. Given the reported effects of propranolol on pain sensitivity in patients with fibromyalgia,^34^ we anticipate β-adrenoreceptor blocking drugs to have an analgesic effect in the short term, and outcome events >4 weeks after the date of the last β-adrenoreceptor blocking drug prescription will not be included in the analysis, except for total joint replacement which may be delayed due to a period of analgesia.

Time to event data in the exposed and unexposed groups will be compared using Kaplan-Meier survival curves. Schoenfeld residuals will be examined to see if survival curves meet the assumptions of the proportional hazard model. Cox proportional HRs and 95% CI will be calculated for each incident outcome using the first Read code for the event. Similarly, HRs will be calculated for new analgesic prescriptions, defined as prescription for NSAIDs, opioids, gabapentin and pregabalin, respectively, in those exposed to β-adrenoreceptor blocking drugs, with unexposed as the referent.

The analysis will be stratified according to class of β-adrenoreceptor blocking drug used. A likelihood ratio test for interactions will be used to examine the hypothesis that the association between β-adrenoreceptor blocking medicines and incident osteoarthritis differs according to statin, aspirin or bisphosphonate prescription, as their use has been negatively associated with osteoarthritis.

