#### Data source

Data from the Clinical Practice Research Datalink (CPRD) will be used in this study. Incepted in 1987, the CPRD is a longitudinal anonymised electronic database containing health records of >10 million people in the UK.^27^ CPRD participants are representative of the UK population in terms of age, sex and ethnicity.^27^ The CPRD contains details of diagnoses and primary care prescriptions. The data are enhanced by linkage with hospitalisation (Hospital Episode Statistics) and mortality records (Office of National Statistics).

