##### Exclusion criteria

Exclusion criteria will be consultation for any of the following prior to the index date:

Osteoarthritis at any joint.Knee, hip, neck or back pain.Conditions causing joint damage or chronic pain: autoimmune inflammatory rheumatic diseases, such as rheumatoid arthritis, psoriatic arthritis, ankylosing spondylitis, lupus, polymyalgia rheumatica, gout, radiculopathy, neuropathy and fibromyalgia.Contraindications to prescription of β-adrenoreceptor blocking medicines: chronic obstructive pulmonary disease, asthma, peripheral vascular disease, heart block, aortic stenosis and hypertrophic obstructive cardiomyopathy.Two consecutive prescriptions for any opioid, any NSAID, gabapentin, pregabalin, duloxetine or amitriptyline prior to the index date.<1 year up-to-standard registration prior to index date to reduce the risk of prevalent cases (eg, with osteoarthritis) being classified as incident cases.^28^

The cohort entry date will be the index date. The unexposed participants will be allocated the index date of their matched exposed participant.

The cohort exit date will be the earliest of the date of the last prescription of β-adrenoreceptor blocking drug prescription, plus 4 weeks or a matched pseudo-exit date for the matched controls, date of the first outcome, date of death, transfer-out date, date of the last data collection or study end date (31 December 2017).

#### Cohort study 2

Cohort study 2 will be on β-adrenoreceptor blocking drug prescription and total joint replacement and analgesic use. The exposure will be as in cohort study 1.

The outcome will be total knee replacement (primary), total hip replacement and analgesic prescription: (1) NSAIDs, (2) opioids, (3) gabapentin or pregabalin, and (4) amitriptyline.

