##### Exclusion criteria

Exclusion criteria will be previous consultation for any of the following prior to the first prescription of β-adrenoreceptor blocking drug:

Osteoarthritis at any other joint.Neck or back pain.Conditions associated with joint damage or chronic pain (as above).Conditions contraindicating prescription of β-adrenoreceptor blocking medicines (as above).Previous knee or hip replacement.Knee or hip joint replacement within 3 months of the date of the first β-adrenoreceptor blocking drug prescription or matched index date in the unexposed participants. These will be excluded because we do not expect β-adrenoreceptor blocking drug prescription to reduce total joint replacement rates immediately and may be commenced during preanaesthetic check-up.<1 year up-to-standard registration prior to the first qualifying prescription of β-adrenoreceptor blocking drug.^28^
Additionally, participants who receive two consecutive prescriptions for opioids, NSAIDs, gabapentin, pregabalin, duloxetine or amitriptyline prior to the index date will be excluded from the cohort when examining the association between β-adrenoreceptor blocking drug prescription and new analgesic prescription.

The cohort entry and exit dates will be as in cohort study 1. Nearest neighbour matching (±0.2 SD) will be used to match exposed to unexposed participants.

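### Total knee and hip replacement are, on the natural reading, identified and dated by the first Read code although hospital records are linked, and the date source for the 3-month exclusion is not clearly set

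*Protocol article*

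**What the plan says.** Four places in the protocol article bear on this.

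- **Cohort study 2, outcomes:** "The outcome will be total knee replacement (primary), total hip replacement and analgesic prescription". Total knee replacement is the primary outcome.
- **Statistical analysis:** "Cox proportional HRs and 95% CI will be calculated for each incident outcome using the first Read code for the event". The only other outcome-specific sentence about hazard ratios concerns new analgesic prescriptions.
- **Data source:** "The data are enhanced by linkage with hospitalisation (Hospital Episode Statistics) and mortality records (Office of National Statistics". Nothing later in the article uses the hospital records to identify or date a replacement.
- **Cohort study 2, Exclusion criteria:** the list opens with "Exclusion criteria will be previous consultation for any of the following prior to the first prescription of β-adrenoreceptor blocking drug". It includes previous knee or hip replacement and also "Knee or hip joint replacement within 3 months of the date of the first β-adrenoreceptor blocking drug prescription or matched index date" in the unexposed. The reason given for the second is that "we do not expect β-adrenoreceptor blocking drug prescription to reduce total joint replacement rates immediately and may be commenced during preanaesthetic check-up".

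**The concern.** A joint replacement is carried out in hospital. The general practice record of it is second-hand, and the date on that record need not be the date of surgery. The article says a direct record is linked, yet the one event rule it states points to the practice code.

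The date matters more here than for most outcomes. The authors expect some patients to start a β-blocker because surgery is imminent, and they guard against this with a window of 3 months. The guard works only as well as the operation date does. If the practice date is used, an operation at week 6 that is first coded in month 4 would pass the exclusion and count as an event in an exposed patient. An operation before the index date that is first coded afterwards could likewise count as new. Operations never coded by the practice would be lost from the primary event count.

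**Working it through.** **1. Which rule covers replacement?** The Statistical analysis section has two outcome-specific Cox sentences: one for each incident outcome, by first Read code, and one for analgesic prescriptions. Replacement is not an analgesic prescription, so by elimination it falls under the Read-code sentence. If it does not, the Cox text names no event source for the primary outcome of cohort study 2.

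**2. Which date governs the exclusions?** The lead-in refers to consultations before the first prescription. Prior replacement fits that and so rests on a consultation record. Prior replacement is listed separately, so the 3-month item must concern operations after the index date. These cannot be prior consultations. Its source is therefore unstated.

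**3. Does the article allow for late coding?** It does for osteoarthritis: the Sensitivity analyses section says the code may come only after several pain consultations, and adds an analysis for this. There is no counterpart for replacement.

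**4. The plan's own figure.** Inputs from Sample size: HR 0.70, 80% power, 1% type I error (two-sided), one exposed to four unexposed, 9 replacements per 1000 person-years.

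Events = (2.576 + 0.842)² / (0.2 × 0.8 × (ln 0.70)²) = 573.8.

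N = 573.8 / 0.009 = 63 752, against 63 753 stated. The figure reproduces. It takes every replacement as captured.

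**5. Illustration of lost events.** The capture share c is an assumption; the documents give none. Events = 573.8 × c. Power = Φ(√(0.16 × events) × |ln 0.70| − 2.576). N for 80% power = 63 752 / c, and the exposed number is N/5.

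| Assumed capture | Events | Power at planned N | N for 80% power | Exposed |
|---|---|---|---|---|
| 95% | 545 | 77% | 67 108 | 13 422 |
| 90% | 516 | 75% | 70 836 | 14 167 |
| 80% | 459 | 68% | 79 691 | 15 938 |
| 70% | 402 | 61% | 91 075 | 18 215 |

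**6. Misdated operations.** At the planned size, with an average of one year of follow-up and 0.009 taken as the unexposed rate, exposed events are 12 751 × 0.009 × 0.70 = 80.3. If 0.009 is instead the rate over both groups, they are 573.8 × 0.14 / 0.94 = 85.5. So the exposed arm carries roughly 80 to 85 events, and each misdated operation adds a little over 1% to that count. The documents do not allow the number of such operations to be estimated.

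**The case against.** **Scope of the rule.** Elsewhere the article attaches the word incident to osteoarthritis and pain, and the Sample size section treats replacement as progression. The authors may not have meant the Read-code sentence to cover replacement, and the full protocol may name hospital procedure codes. This has force. However, the article does not simply leave the matter open: it states one rule and makes no exception for the primary outcome. On either reading the source needs stating.

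**Safeguards already present.** Exposure needs two prescriptions no more than 60 days apart, which removes patients given a single perioperative prescription. One year of prior registration limits misclassified earlier operations. Matching on GP surgery means that practice-level under-recording is shared within matched sets, and equal under-recording leaves the hazard ratio largely unchanged. All of this stands. Matching does not, however, deal with the preanaesthetic starts, because there it is the planned operation that creates the exposure.

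**Power.** The article cites 40 560 potentially eligible exposed patients against 12 755 needed. Even 70% capture would need only 18 215, so lost events alone are no serious threat.

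**Stronger readings that the documents do not support.**

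- A reader might infer that the 3-month rule is tied to the practice coding date. The article does not say so.
- A reader might infer that the knee replacement hazard ratio is pushed upwards by a definite amount. Misdated preanaesthetic starts would act in that direction, against the hypothesised benefit, but their number is unknown. Unequal under-recording could act either way.
- A reader might want hip replacements after fracture censored. The outcome is total hip replacement with no restriction by cause, so this would change what a secondary outcome measures.

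**Conclusion.** The point holds as a weakness in how the cohort study 2 primary event is identified and dated. On the natural reading, a hospital procedure is taken from the GP record while a linked hospital record goes unused, and the exclusion that guards against reverse causation has no clearly set date source.

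The harm is conditional. It requires that the GP record is in fact used, and that practices sometimes code operations late or not at all. The documents give neither a lag nor a capture rate, so no bias in the hazard ratio can be stated. The power figures of 61% to 77% apply to assumed capture of 70% to 95% at the planned size, and the available exposed population could offset that loss. The change is worth making because it concerns a primary outcome and the article's own safeguard, and it uses data the article already describes as linked.

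**What to change.** State one source and date rule for knee and hip replacement, and apply it in three places: the outcome, the prior-replacement exclusion and the 3-month window. In practices with hospital linkage, use the hospital procedure date. Use the first Read code only where there is no linkage. Add a sensitivity analysis restricted to linked practices. Reword the exclusion list so that the 3-month item no longer sits under a lead-in about earlier consultations.

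The cost should be modest programming, but the article does not say what share of practices is linked. If linkage is incomplete, the linked-only analysis will be smaller and ascertainment will differ between practices. Because matching is within GP surgery, ascertainment stays the same within each matched set, provided linkage is decided practice by practice.

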### Sample size

#### Incident knee osteoarthritis and hip osteoarthritis

The incidence of knee and hip osteoarthritis is 6.5 and 2.1 per 1000 person-years in primary care-based European populations >40 years in age.^1^ Previous research suggests that 6.14% of patients registered in the CPRD are on β-adrenoreceptor blocking drugs, with over two-thirds on treatment for >10 years.^38^ Thus, for a cohort with one exposed and four unexposed participants, the total sample size required to detect an HR of 0.70 for developing knee osteoarthritis and hip osteoarthritis is 88 273 (17 655 exposed) and 273 225 (54 645 exposed) participants, respectively, for a planned study with 80% power and 1% type I error.

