#### Progression to joint replacement surgery

The incidence of total knee replacement in community-dwelling adults with knee pain is 9 per 1000 person-years ([name] thesis, University of Nottinghampublished on university website, 2012), and clinical experience suggests that hip osteoarthritis progresses more rapidly ([name]). Thus, for a cohort with one exposed and four unexposed participants, the total sample size required to detect an HR of 0.70 for total knee replacement in the exposed participants is 63 753 with 80% power and 1% type I error. As 3.38% of community-dwelling adults with clinically defined knee osteoarthritis are on β-adrenoreceptor blocking drugs (Knee Pain in the Community Study, 2014–2015, [name], unpublished data), and given a population prevalence of knee pain of 20% in those over 40s, this gives a potentially eligible exposed population of 40 560 from which to choose 12 755 exposed participants in the CPRD.

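### The three sample-size totals are person-years labelled as participants, so the stated 80% power holds only if mean follow-up is one year

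*Protocol article*

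**What the plan says.** In the protocol article, under *Incident knee osteoarthritis and hip osteoarthritis*, the inputs are a pair of rates ("The incidence of knee and hip osteoarthritis is 6.5 and 2.1 per 1000 person-years in primary care-based European populations"), a 1:4 design ("for a cohort with one exposed and four unexposed participants"), and "for a planned study with 80% power and 1% type I error". From these the article derives "the total sample size required to detect an HR of 0.70 for developing knee osteoarthritis and hip osteoarthritis". The answer is given in people and not in person-years: it "is 88 273 (17 655 exposed) and 273 225 (54 645 exposed) participants, respectively". Just before the totals, the text describes people currently prescribed β-blockers, "with over two-thirds on treatment for >10 years".

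Under *Progression to joint replacement surgery* the same steps are repeated for Study 2: "The incidence of total knee replacement in community-dwelling adults with knee pain is 9 per 1000 person-years", and the total for HR 0.70 is 63 753, of whom 12 755 are exposed. On supply, a 20% prevalence of knee pain and 3.38% β-blocker use are combined, and the result, 40 560, is introduced with "this gives a potentially eligible exposed population of".

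Follow-up is defined elsewhere. The *Exclusion criteria* of Cohort study 1 end it at the last β-blocker prescription plus 4 weeks, or at a matched pseudo-exit date for controls, if nothing else ends it sooner. Cohort study 2 adopts the same exit dates. *Statistical analysis* applies the last-prescription rule to osteoarthritis, pain and new analgesic outcomes, but keeps later joint replacements.

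**The concern.** Events divided by events per person-year give person-years. Calling the result participants assumes exactly one year of observation each, and no such assumption appears in the article. The only duration quoted in the section, treatment beyond 10 years in most current users, does not enter the arithmetic.

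The unit matters because follow-up in this design is tied to how long treatment lasts. Entry needs only two prescriptions no more than 60 days apart, osteoarthritis follow-up stops shortly after the last one, and one of the planned exposure categories is treatment of six months or less. Power at a given number of people therefore depends on a quantity that the calculation leaves out. As printed, the totals cannot be used to judge whether either cohort is large enough for its primary outcome.

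**Working it through.** **Inputs, all from the Sample size section.** HR 0.70; power 80%; type I error 1% (sidedness not stated; two-sided reproduces the figures); exposed share 1/5 = 0.2; yearly incidence 0.0065 (knee osteoarthritis), 0.0021 (hip osteoarthritis) and 0.009 (total knee replacement).

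**Step 1: required events (Schoenfeld).**
D = (z₀.₉₉₅ + z₀.₈₀)² / [p(1 − p)(ln HR)²] = (2.5758 + 0.8416)² / [0.2 × 0.8 × (ln 0.70)²] = 573.77, or 574 rounded up.

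**Step 2: reproduce the plan's totals.**

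| Outcome | D / yearly rate | Stated total |
|---|---|---|
| Knee osteoarthritis | 573.77 / 0.0065 = 88 272.6 | 88 273 |
| Hip osteoarthritis | 573.77 / 0.0021 = 273 224.7 | 273 225 |
| Total knee replacement | 573.77 / 0.009 = 63 752.4 | 63 753 |

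Rounded up, all three match exactly. Other methods do not fit for knee osteoarthritis: a one-sided 1% test gives 75 855, a comparison of two proportions at 1:4 gives 110 885 (114 065 with continuity correction), and Freedman's formula with unequal allocation gives 717 or 468 events instead of 573.8.

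**Step 3: power of 88 273 people for knee osteoarthritis, by follow-up.** The article gives no mean follow-up, so T is an assumption: everyone is followed for T years at a constant hazard. With the quoted incidence r as the pooled rate, events = 88 273 × (1 − e^(−rT)). With r as the unexposed rate, the exposed fifth has hazard 0.7r. Power = Φ(√(0.16 × events) × |ln 0.70| − 2.5758).

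| T (years) | Events, pooled | Power, pooled | Events, unexposed reading | Power, unexposed reading |
|---|---|---|---|---|
| 0.5 | 286 | 44% | 269 | 41% |
| 1 | 572 | 80% | 538 | 77% |
| 2 | 1140 | 98.8% | 1072 | 98.2% |
| 3 | 1705 | >99.9% | 1603 | 99.9% |

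The hip osteoarthritis and total knee replacement totals give almost the same power at each T.

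**Step 4: participants needed for 574 knee osteoarthritis events, pooled reading.** 176 903 at 0.5 year; 88 596 at 1 year; 44 442 at 2 years; 29 724 at 3 years.

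**Step 5: person-years if the quoted incidence is the unexposed rate.** The blended rate is (0.8 + 0.2 × 0.7) = 0.94 of it. Then 573.77 / (0.94 × 0.0065) = 93 907; 573.77 / (0.94 × 0.0021) = 290 665; 573.77 / (0.94 × 0.009) = 67 822.

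**Step 6: exposed counts.** 88 273 / 5 = 17 654.6 and 273 225 / 5 = 54 645, as printed. 63 753 / 5 = 12 750.6, so one fifth is 12 751, not 12 755.

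**The case against.** The strongest reply concerns direction. A reader might infer from the 41% to 44% figures that the study is underpowered, and the article does not support that. Its only duration figure points to follow-up well above one year. That figure comes from current users, so it overstates persistence among people entering at a first prescription, but if just half of the exposed stayed in follow-up for two years the mean would already reach one year. The six-month exposure category is a cut-point, not a forecast. For joint replacement, *Statistical analysis* lets follow-up run past the last prescription, which makes a very short mean least plausible there. All of this stands: no passage supports a mean of half a year, and none rules it out.

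Four further inferences also go too far:

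- **Rate applied to the wrong group.** The article does not describe the quoted incidence as an unexposed rate, so using it as the overall rate is defensible. The 0.94 factor is one reading, not a correction.
- **Supply overstated.** The exclusions, and the requirement that the osteoarthritis consultation come before the first prescription, shrink the pool behind 40 560. However, that figure uses current use from a 2014–2015 source, whereas the cohort spans 1990 to 2017, and it counts knee disease only although hip osteoarthritis also qualifies. The net direction is not established, and the text already says potentially eligible. The base population behind the product is a detail that a condensed article may omit.
- **Loss of power from fewer than four controls.** No expected match rate is given, so there is nothing to calculate from.
- **The 12 755 figure.** It is four people away from one fifth of the total and has no consequence of its own.

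None of this removes the unit error. The article prints both its inputs and its results, and they are dimensionally inconsistent. That is a stated error, not an omission caused by condensing.

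**Conclusion.** Wrong as written, and cheap to correct. The totals of 88 273, 273 225 and 63 753 are person-years. As numbers of participants they deliver the stated 80% power only at a mean follow-up of about one year, with the quoted incidence read as the pooled rate. They are conservative if mean follow-up is longer and insufficient if it is shorter, and the article does not settle which applies under the last-prescription-plus-4-weeks exit. The reproduction of the totals needs only the plan's own inputs and a two-sided test. The power range also assumes a constant hazard and a common follow-up time. The error leaves the estimand and the analysis untouched, but it affects the sample-size basis of both primary outcomes.

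**What to change.** 1. State the target as about 574 events per outcome, or as about 88 300 (knee osteoarthritis), 273 200 (hip osteoarthritis) and 63 800 (total knee replacement) person-years.
2. Say whether each quoted incidence is the pooled or the unexposed rate. If unexposed, the person-years become about 93 900, 290 700 and 67 800.
3. Convert to participants with an explicit assumed mean follow-up for each outcome, and show power over a range such as 0.5 to 3 years.
4. Before doing this for total knee replacement, reconcile the exit date that Cohort study 2 takes over from Cohort study 1 with the censoring rule in *Statistical analysis*.
5. Recompute the exposed count for Study 2 from the revised total, so that it agrees with the 1:4 ratio.
6. Describe 40 560 as a rough figure before exclusions, based on knee pain prevalence and current use, and not as a count of eligible new users.

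The cost is a rewrite of the Sample size section with one stated follow-up assumption per outcome. Relabelling the totals does not itself call for more participants, and the planned analysis does not change.

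### The printed sample sizes are really person-years, and that many person-years gives about 67% power for HR 0.70 at two-sided 1%, not 80%; power for that many participants depends on a mean follow-up the plan does not state

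*Protocol article*

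**What the plan says.** The protocol article sizes three outcomes under Sample size.

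- **Incident knee and hip osteoarthritis.** The rates are given as "The incidence of knee and hip osteoarthritis is 6.5 and 2.1 per 1000 person-years in primary care-based European populations >40 years in age". The design is described as "for a cohort with one exposed and four unexposed participants". The effect to be detected is HR 0.70. Taking knee and then hip, the printed requirement "is 88 273 (17 655 exposed) and 273 225 (54 645 exposed) participants". The error rates behind both figures are worded "for a planned study with 80% power and 1% type I error".
- **Progression to joint replacement surgery.** The rate is introduced as "The incidence of total knee replacement in community-dwelling adults with knee pain is 9 per 1000 person-years". On the same 1:4 design, power and type I error, the figure printed is 63 753, of whom 12 755 are exposed. It is introduced by the words "the total sample size required to detect an HR of 0.70 for total knee replacement in the exposed participants is".

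The section does not state a formula, whether the test is one- or two-sided, a mean follow-up, or which exposure group the incidences describe. The only statement there about duration is that "6.14% of patients registered in the CPRD are on β-adrenoreceptor blocking drugs, with over two-thirds on treatment for >10 years".

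**The concern.** A rate per 1000 person-years turns a required number of events into person-years. It gives participants only when multiplied by a follow-up time, and none appears. Two further inputs also look inconsistent with the HR of 0.70 being sized for: the same incidence seems to be applied to both groups, and the exposed share of events seems to be set at the exposed share of participants, which is true only when the HR is 1.

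The calculation supports both primary outcomes (knee osteoarthritis in cohort study 1, total knee replacement in cohort study 2) and hip osteoarthritis. If the stated 80% does not belong to the stated totals, a reader cannot tell how much weight a null result at the 1% level would carry.

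**Working it through.** **Inputs (Sample size section).** HR 0.70; exposed share 0.20; type I error 1%; power 80%; rates 0.0065, 0.0021 and 0.009 per person-year. Two-sided testing is inferred: it reproduces the printed totals, and one-sided testing does not (it gives 75 855, 234 789 and 54 784).

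**Step 1: reproduce the plan.** Schoenfeld events:

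D = (2.5758 + 0.8416)² / (0.20 × 0.80 × (ln 0.70)²) = 573.77

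| Outcome | Division | Result | Printed |
|---|---|---|---|
| Knee osteoarthritis | 573.77 / 0.0065 | 88 272.6 | 88 273 |
| Hip osteoarthritis | 573.77 / 0.0021 | 273 224.7 | 273 225 |
| Total knee replacement | 573.77 / 0.009 | 63 752.4 | 63 753 |

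All three agree to the unit after rounding up. The printed figures are person-years, or equivalently participants followed for exactly one year, with one incidence for everyone.

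**Step 2: expected events under HR 0.70.** With rate r in the unexposed and 0.70r in the exposed, the cohort rate is r × (0.80 + 0.20 × 0.70) = 0.94r. Expected events are 0.94 × 573.77 = 539.3. The exposed share of events is 0.14 / 0.94 = 14.9%, about 80 exposed and 459 unexposed.

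**Step 3: power at the printed number of person-years.**

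- Event shortfall alone, in the plan's own formula: √(539.3 × 0.16) × 0.3567 − 2.5758 = 0.737, so power is 77.0%.
- Event split as well, with a log-rank (score) calculation and p = 0.149: [539.3 × (0.20 − p) / √(539.3 × 0.16) − 2.5758] / √(p(1 − p) / 0.16) = (2.965 − 2.576) / 0.890 = 0.437, so power is 66.9%.
- Poisson simulation, 400 000 runs: about 67% by score and Wald tests, 70% by likelihood ratio. Cox simulation, 3000 replicates at one year each: 67.1%, 67.0% and 66.1% for the three outcomes.

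The result is the same for all three outcomes because each total is scaled to the same number of events.

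**Step 4: which population the incidence describes.**

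| Reading of the quoted incidence | Events | Power (score) |
|---|---|---|
| Unexposed rate | 539 | 66.9% |
| General population, 6.14% exposed | 549.5 | 68.0% |
| Average over the matched cohort | 573.8 | 70.6% |

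**Step 5: power for the printed totals read as participants** (quoted incidence taken as the unexposed rate).

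| Mean follow-up, years | Power (score) |
|---|---|
| 1 | 66.9% |
| 1.26 | 80.1% |
| 1.5 | 88.2% |
| 2 | 96.5% |
| 3 | 99.8% |

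**Step 6: person-years for 80%.** The multiplier is about 1.26: 1.26 × 88 273 = 111 224; 1.26 × 273 225 = 344 264; 1.26 × 63 753 = 80 329. Rounded up, these are about 111 500, 345 000 and 80 500. Simulated power at 1.26 is 80% by score and Wald tests. The closed Wald formula with variance 1/d1 + 1/d0 is more conservative: it gives 64.6% at the printed person-years and needs a multiplier of about 1.35.

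**Step 7: exposed count.** 88 273 / 5 and 273 225 / 5 give the printed 17 655 and 54 645. But 63 753 / 5 = 12 750.6, so 12 751, where 12 755 is printed.

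**The case against.** The strongest reply is that the totals are printed as participants and nothing in the article fixes follow-up at one year. Data run from 1990 to the end of 2017, most users are said to be treated for more than 10 years, and under Statistical analysis joint replacement is not censored at the last prescription. If mean follow-up exceeds about 1.26 years, the printed totals deliver 80% or more. This stands. A reader might infer from the 67% that the planned study would miss a true HR of 0.70 about one time in three. The documents do not support that, because it holds only at about one person-year per participant.

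The reply does not rescue the statement as written. The follow-up that would justify 80% is neither stated nor used in the calculation, and in cohort study 1 it is uncertain: follow-up stops four weeks after the last prescription, and two prescriptions within 60 days are enough to qualify.

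Two further points have weight. The incidences are described as population rates, not unexposed rates, so the drop to 539 events is one reading; on the others, power is 68% to 71%. And Schoenfeld's formula is standard and was evaluated correctly, so the weakness is an approximation that is optimistic when the smaller group has the lower hazard, rather than a slip of arithmetic.

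Finally, the cohort comes from an existing database with no stated cap at these totals, and the article counts 40 560 potentially eligible exposed people for total knee replacement, about 3.2 times the number it needs. That limits the practical consequence.

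**Conclusion.** The point holds in conditional form. As person-years, which is the only unit the arithmetic supports, the printed totals give about 67% power at two-sided 1% if the quoted incidence is the unexposed rate, and about 70-71% if it is the matched-cohort average. No reading tried reaches 80%. Most of the loss comes from the event split (77% to 67%); the lower event count accounts for the first three points (80% to 77%).

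These figures assume two-sided testing, constant hazards and independent observations. As participants, the same totals have no determinate power until a mean follow-up is given. The study may well be adequately powered; what is wrong is that the stated 80% does not follow from the stated inputs. The exposed count of 12 755 is a separate slip of four people with no bearing on power.

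**What to change.** In the Sample size section:

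1. State the test as two-sided and say which group each incidence describes.
2. Restate the requirement in person-years, with rate r in the unexposed, 0.70r in the exposed and the variance under the alternative: about 111 500 (knee osteoarthritis), 345 000 (hip osteoarthritis) and 80 500 (total knee replacement). These match a log-rank calculation or simulation. If the closed Wald formula is preferred, say so, since it asks for about 1.35 rather than 1.26 times the printed figures.
3. Convert to participants with a stated mean follow-up, separately for outcomes censored four weeks after the last prescription and for joint replacement. If the printed totals are kept, give their power as about 67% only on the condition that each participant contributes one person-year.
4. Correct the exposed count for total knee replacement to 12 751.

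The cost is rewording and a short recalculation. No new data are needed, and the eligibility criteria, matching and analysis are unchanged.
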